### 9.3 Patient-Reported Outcomes

**Administering Study Assessments.** Each participant will be instructed to download the MyDataHelps app on their personal smartphone or can use the web version of MyDataHelps on the study-provided tablet. They will be required to create an account on MyDataHelps. Enrolled participants with the app on their smartphone will receive notifications, emails, or texts to complete study measures per protocol.

For those who are not using the MyDataHelps app on their smartphone or tablet, notifications to complete questionnaires will be sent via email or text. E-mail is required for participants who are unable to use the MyDataHelps app on their smartphone and who do not have access to text notifications, so that they know to complete surveys on the MyDataHelps website. Participants who need to receive email notifications about available surveys but who do not have an email account will be assisted in obtaining a free Gmail account and how to access it on their computer tablet by study staff.

**The validated instruments used in this study are as follows (See Appendix A):**

*Brief Pain Inventory (BPI):* The BPI is a 17-item patient self-rating scale that assesses sensory and reactive components of pain. For sensory components, it addresses severity, location, chronicity, and degree of relief due to therapy. For reactive components, it assesses depression, suffering, and perceived availability of relief. Reliability has been demonstrated over short intervals using test retest item correlation; worst pain,  $r=0.93$ , usual pain,  $r=0.78$ , pain now  $r=0.59$ . It has been validated in patients with both cancer and non-cancer pain. Ratings of pain interference with various activities increased as ratings of pain severity were higher. The proportion of patients receiving opioid analgesics also increased with increased severity rating.

The BPI uses 0 to 10 numeric rating scales for item rating because of its simplicity and lack of ambiguity. Since pain can be variable over a day, the BPI asks patients to rate their pain at the time of completing the questionnaire, and also at its worst, least, and average over the previous 7 days. The primary endpoint for this clinical trial will be based on the 7-day worst joint pain as reported on the BPI. The ratings can be combined to give a composite index of pain severity. Also, using numeric 0 to 10 scales, with 0 being “no interference” and 10 being “interferes completely”, the BPI asks for ratings of the degree to which pain interferes with mood, walking and other physical activity, works, social activity, relations with others, and sleep. The mean of these scores can be used as a pain interference score. This will be completed at baseline, 6, and 12 weeks (and off study if patient discontinues before week 12).

*PROMIS-29+2 Profile v2.1:* A validated questionnaire that assesses patient-reported symptoms over the past 7 days in 9 PROMIS domains (fatigue, sleep disturbance, physical functioning, depression, anxiety, ability to participate in social roles and activities, cognitive function-abilities, and pain intensity and interference). Raw scores for each domain are calculated and then converted to a

T-score, with a mean of 50 and a standard deviation of 10. Higher T scores represent more of the concept being measured. This 31-item questionnaire will be completed at baseline, 6 and 12 weeks (and off study if patient discontinues before week 12).

*Global Ratings of Change (GRC) Scale:* This is a single-item measure to assess the overall change in pain and stiffness since starting study treatment. It is a 7-point Likert scale from -3 to +3. This will be completed at 6 and 12 weeks (and off study if patient discontinues before week 12).

*Mao Expectancy of Treatment Effect (METE):* The METE is a validated 4-item self-report questionnaire rated on a scale of 1-5 (from total disagreement to total agreement), which assesses a patient's expectation that acupressure will relieve her AIMSS symptoms. The instrument had good internal consistency (Cronbach's  $\alpha$  0.95) in a prior study of acupuncture in patients with cancer. Will be completed at baseline.

*Fibromyalgia (FM) Survey:* The FM survey is a combined measure of widespread pain (body map of painful sites) and symptom severity (e.g., fatigue, cognitive problems, headache, poor mood, scores range 0-12), as a self-reported proxy of centralized pain, assessed at baseline. This is a continuous measure with scores ranging from 0-31. Will be completed at baseline.

*Massachusetts General Hospital Acupuncture Sensation Scale (MASS):* consists of twelve predefined descriptors and one subjective component specified by the subjects in their own words to measure levels of *de qi* sensations. *De qi* is a prerequisite term in Traditional Chinese Medicine used to describe sensory stimulation. It has historically been thought to be an indicator of appropriate acupuncture or acupressure treatment and thus relates to therapeutic effectiveness.

In addition to these validated questionnaires, two non-validated surveys will be used to collect information:

*Demographics Questionnaire:* This 5-item survey will be used to collect basic information about sex, race/ethnicity, education, marital status, and income. Participants are given the option of not answering each of the questions.

*Post-intervention Survey:* This non-validated survey will ask participants what type of acupressure they thought they were performing (relaxing acupressure or sham acupressure), whether they felt the benefits they received were worth the time spent performing acupressure, whether they would recommend this intervention to others, and whether they used the AcuWand device.

## **9.4 Stool samples**

### **9.4.1 Collection**

Patients will be given the necessary supplies to collect stool samples using manufacturer protocols and mail them to the cancer center using UPS or USPS mailers (see Appendix B and C).

#### **9.4.2 Method**

Samples will be analyzed according to standard methods by the UM Microbiome Core. The method to be used is their standard 16S protocol that targets and amplifies the V4 region of bacterial and archaeal 16S rRNA-encoding genes.

### **10 CRITERIA FOR EVALUATION AND ENDPOINT**

#### **10.1 Safety**

Few adverse events are expected in this non-pharmacologic, non-invasive interventional study. Routine safety and tolerability will be evaluated by the study coordinator.

#### **10.2 Stopping Rules**

N/A

### **11 STATISTICAL CONSIDERATIONS**

#### **11.1 Statistical hypothesis**

Use of true self-acupressure for 12 weeks in postmenopausal women with breast cancer who are experiencing AIMSS will result in improvement in joint pain compared to sham self-acupressure for 12 weeks.

#### **11.2 Sample size determination**

With a sample size of 44 evaluable participants (22 evaluable per arm), assuming a standard deviation of difference in worst pain score between treatment groups of 2.3 points, we will have 80% power to detect a reduction of 2 points in worst pain on the BPI at 12 weeks, assuming a 5% significance level. A 2-point improvement in pain is considered a minimal clinically important difference. A total of 50 participants will be enrolled to account for potential dropout, to ensure 44 participants are evaluable for the primary endpoint.

#### **11.3 Statistical Analyses**

##### **11.3.1 Primary endpoint**

All demographic, clinical and outcome variables will be described using means, standard deviations, frequencies and proportions for the full sample and by treatment group.

The primary endpoint is change in worst joint pain (range 0-10) with 12 weeks of the intervention. A linear model using generalized estimating equations with robust variance will be used with a treatment group, time and a time by group interaction to determine the difference between true acupressure and sham acupressure. We will use an identity link function employing a transformation if needed on the outcome. We will assess the success of blinding by comparing the proportion of participants

who believed they had received true acupressure across groups using a chi-square test.

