## **5 STRATIFICATION FACTORS**

None

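### The primary model compares unadjusted change scores; adjusting for baseline worst joint pain would give a modest, nearly free gain in precision

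*Protocol*

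**What the plan says.** Protocol Section 11.3.1 gives the endpoint ("The primary endpoint is change in worst joint pain (range 0-10) with 12 weeks of the intervention") and a linear GEE model with robust variance that "will be used with a treatment group, time and a time by group interaction to determine the difference between true acupressure and sham acupressure". No other term is listed. The secondary-endpoint subsection that follows (numbered 12.3.2) applies the same kind of model to average pain, pain interference and the PROMIS outcomes.

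Section 11.2 plans for 22 evaluable participants per arm, "assuming a standard deviation of difference in worst pain score between treatment groups of 2.3 points", and states that "we will have 80% power to detect a reduction of 2 points in worst pain on the BPI at 12 weeks", "assuming a 5% significance level".

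Section 5, headed "STRATIFICATION FACTORS", lists none. Section 6.3 uses blocks of 2 or 4, which balance numbers but not pain. The BPI is scheduled at baseline (Sections 8 and 9.3), so baseline worst pain will be available at no extra effort.

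**The concern.** Subtracting baseline is not the same as adjusting for it. A change score fixes the slope of follow-up on baseline at 1. When the true slope is below 1, participants who start higher tend to fall further whatever their arm. Two things follow:

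- The arm that happens to start higher appears to improve more.
- The estimate is noisier than one that conditions on baseline.

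With 22 per arm and no stratification on pain, a chance baseline difference of half a point is common. At stake are some precision and some protection against that imbalance. The validity of the test is not in question.

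**Working it through.** **1. Reproduce the stated power.** Inputs (Section 11.2): 22 per arm, difference 2, SD 2.3, significance level 5%. I read 2.3 as the per-patient SD of change and the test as two-sided; Section 11.2 settles neither explicitly.

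- SE of the contrast = 2.3 × √(2/22) = 0.69; noncentrality = 2/0.69 = 2.88.
- Two-sided noncentral-t power on 42 df = 80.4%. With 21 per arm it is 78.5%, so 22 is the smallest number reaching 80%. A one-sided test would give about 88%.

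The 80% is therefore the power of an unadjusted two-sample comparison.

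**2. What the listed terms estimate.** With baseline and week 12 both in the response and complete data, the group-by-time coefficient is the raw difference in mean change. A simulated data set of 44 gave −0.8445 both ways. If change itself is the response, there is still no baseline term. Either way baseline is only subtracted.

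**3. Gain from adjustment, using Table 1 (Section 2.2, BPI severity).** Let s0, s1 and sc be the SDs at baseline, at follow-up and of change.

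- Correlation r = (s0² + s1² − sc²)/(2·s0·s1)
- Slope b = r·s1/s0
- Adjusted variance = s1²(1 − r²), divided by sc² for the ratio

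Example (acupressure, week 6): r = (2.56 + 4.84 − 4.00)/(2 × 1.6 × 2.2) = 0.483; adjusted variance = 4.84 × (1 − 0.233) = 3.71; ratio = 3.71/4.00 = 0.93.

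| Row | s0, s1, sc | r | b | Ratio | 2.3 becomes | Power (41 df) |
|---|---|---|---|---|---|---|
| Acupressure, week 6 | 1.6, 2.2, 2.0 | 0.48 | 0.66 | 0.93 | 2.22 | 83.2% |
| Usual care, week 6 | 1.8, 2.1, 2.0 | 0.48 | 0.56 | 0.85 | 2.12 | 86.5% |
| Acupressure, week 10 | 1.6, 2.2, 1.8 | 0.59 | 0.81 | 0.97 | 2.27 | 81.5% |
| Usual care, week 10 | 1.8, 2.2, 1.6 | 0.70 | 0.85 | 0.97 | 2.27 | 81.5% |

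The variance falls by about 3-15%. For pain interference, a secondary outcome under the same kind of model, the same formulas give ratios of 0.58 and 0.83 at week 6 and 0.94 and 0.86 at week 10 (acupressure, usual care).

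**4. Effect of chance imbalance.** With baseline SD 1.6-1.8, the SE of the between-arm baseline difference is 1.6 × √(2/22) = 0.48 to 1.8 × √(2/22) = 0.54. A difference of at least 0.5 points then occurs in about 30-36% of trials. Each 0.5 points shifts the change-score estimate by 0.5 × (1 − b):

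- Smallest: 0.5 × (1 − 0.852) = 0.07
- Largest: 0.5 × (1 − 0.563) = 0.22

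Against the SE of 0.69 this is about 0.1 to 0.3 of a standard error.

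**The case against.** The strongest reply is that nothing here is wrong. The planned test is unbiased over repeated randomisations and reaches its own power target. The endpoint already removes most of the effect of baseline, and the remaining shift is small beside a 2-point target. All of that stands. It makes this a suggested improvement, not an error.

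The reply also says that a covariate list often sits in a SAP, and that the missing-data paragraph in Section 11.3.2 mentions covariates. This carries only part of the way. The protocol names its model terms, and a SAP that added baseline would depart from them. It is fair, however, that the protocol does not say whether baseline is in the response, whether time is categorical, or whether the weekly scores enter. The power figures above assume a single baseline-to-week-12 contrast.

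Three stronger readings are tempting, and the documents do not support them.

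- **A large loss of power.** If baseline and follow-up SDs were equal, a correlation of 0.48 would give a variance ratio of (1 + 0.48)/2 = 0.74 and power of about 90%. Table 1 severity SDs are not equal: they rise from 1.6-1.8 to 2.1-2.2. Using only the week-6 rows would also overstate the gain, because the week-10 rows, although after washout, give 3%.
- **The entry threshold biases the comparison.** Section 4.1.4 requires worst pain of at least 4, but regression to the mean affects both arms. The threshold is applied at screening, up to 4 weeks before the separate baseline measurement (Section 8), so part of that regression occurs before change is measured.
- **The sample size is wrong.** It is not; the 80% reproduces without adjustment.

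**Conclusion.** The point holds as a modest gain in precision and robustness. The primary analysis is valid and meets its stated 80% power. Adjusting for baseline would lower the variance by about 3-15%, for power of about 81.5-86.5%, and would remove a dependence on chance imbalance worth about 0.07-0.22 points per 0.5 points of baseline difference. The upper end is not negligible beside the 0.92-point adjusted true-versus-sham difference that Section 2.2 reports for the acupuncture trial, but it is small against the 2 points planned for here.

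The direction is secure: in large samples with 1:1 allocation, linear adjustment for baseline has variance no greater than the change score. The size is not secure. It rests on reading 2.3 as the SD of change. It also rests on week-12 worst pain in AI users against sham behaving like the pilot's BPI severity at weeks 6 and 10, measured against usual care in women not taking AIs. The protocol gives no baseline-to-week-12 correlation for worst pain.

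**What to change.** Before unblinding, amend Section 11.3.1 in one of two ways:

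- add baseline worst joint pain as a covariate, with post-baseline scores as the response; or
- keep baseline in the response and constrain the baseline means to be equal across arms.

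Name the adjusted week-12 contrast as the primary result. Do the same for average pain, pain interference and the PROMIS domains, each with its own baseline.

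The cost is a sentence or two of text and one degree of freedom. No new data or participants are needed and the sample size can stand. Fixing this in advance also avoids a disputed post-hoc adjustment if the arms differ at baseline.

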### **12.3.2 Secondary endpoints**

1. The proportion of patients who have at least a 2-point reduction in *worst and average* pain from baseline to 12 weeks will be reported with the corresponding exact binomial confidence intervals in each treatment group. The proportions will be compared using a chi-square test for each outcome. Differences from baseline at each time point for worst pain will be summarized via mean and standard deviation. Linear models using generalized estimating equations will assess the change in average and worst pain over time between groups similar to the primary endpoint.
2. Differences from baseline at each time point for pain interference (range 0-10) will be summarized via mean and standard deviation. Linear models using generalized estimating equations will assess the change in pain interference over time between groups similar to the primary endpoint.
3. Descriptive statistics including mean, standard deviation, median, interquartile range, t tests, and chi squared tests will be used to describe all other patient-reported outcomes (sleep disturbance [range 32-73.3], fatigue [range 33.7-75.8], physical function [range 22.5-57], anxiety [range 40.3-81.6], depression [range 41-79.4], and cognitive function [range 29.4-61.2] over time), as appropriate. Patient reported outcomes will be analyzed using linear models and generalized estimating equations with robust variance similar to the primary outcome. Normalizing transformations will be used if necessary to ensure accurate model fit.
4. Adherence to the intervention will be assessed through the trial and reported using descriptive statistics. Adherence will be calculated based on number of days acupressure is performed and number of minutes of acupressure performed each day. The proportion of participants who are fully adherent will be compared between groups using a chi-square test.
5. Safety will be assessed throughout the trial and adverse events will be reported using descriptive statistics.

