| Study Center(s)     | Single-center                                                                                                                                                                                                                                                                                                                                                                                                                                                                                                                                                                                                                                                                                                                                                                                                                                                                                                                                                                                                                                                                                                                                                   |
| Objectives          | 
Primary Objective:
 
To determine the effect of 12 weeks of true acupressure versus sham acupressure on AI-associated worst joint pain, as assessed with the Brief Pain Inventory (BPI)
 
Secondary Objectives:
 
To determine the effect of 12 weeks of true acupressure versus sham acupressure on other AI-associated pain symptoms, including average pain and pain interference, as assessed with the BPI
 
To determine the effect of 12 weeks of true acupressure versus sham acupressure on other AI-associated symptoms, including anxiety, depression, insomnia, and cognitive function, as assessed with the PROMIS-29+2 Profile
 
To examine the adherence with 12 weeks of true acupressure versus sham acupressure in patients with breast cancer taking aromatase inhibitor therapy
 
Exploratory objectives:
 
To examine the association between expectation of response to acupressure as assessed with the METE and observed response based on change in BPI worst pain score
 
To examine the impact of 12 weeks of true acupressure versus sham acupressure therapy on
 |

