### **1.2 Secondary Objectives**

1. To determine the effect of 12 weeks of true acupuncture versus sham acupuncture on other AI-associated pain symptoms, including average pain and pain interference, as assessed with the BPI.

*Endpoint: Change in (a) average joint pain and (b) pain interference with 12 weeks of the intervention*

2. To determine the effect of 12 weeks of true acupuncture versus sham acupuncture on other AI-associated symptoms, including anxiety, depression, insomnia, and cognitive function, as assessed with the PROMIS-29+2 Profile.

*Endpoint: Change in (a) anxiety, (b) depression, (c) sleep disturbance, (d) fatigue, and (e) cognitive function with 12 weeks of the intervention*

3. To examine the adherence with 12 weeks of true acupuncture versus sham acupuncture in patients with breast cancer taking aromatase inhibitor therapy.

*Endpoint: Number of days acupuncture is performed during the 12 weeks of the intervention*

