Mean age was  $59.0 \pm 7.2$ , 100% of the women were Caucasian and 53% were post-menopausal. There were no significant differences in chronic pain medications (e.g., NSAIDs, opioids, acetaminophen, anticonvulsants, antidepressants) between groups. Changes in pain and percentage of participants who experienced clinically significant changes are shown below in Table 1 and Figure 1. Adherence to performing acupressure treatments as recorded in logbooks was  $79.8 \pm 22.9\%$  (34 out of 42 total treatments), and 53 out of 74 women (72%) completed at least 70% of their acupressure treatments. Fidelity was  $89.2 \pm 14.4\%$  half-way through the acupressure intervention (at week 3), and had improved to  $94.6 \pm 10.2\%$  at week 6.

[figure not shown]

**Figure 1.** Percent of participants who had a clinically significant reduction in self-reported pain (Blue: relaxation acupressure, Red: usual care)

| Table 1 Change In Brief Pain Inventory (BPI) Pain Severity and Interference |                                   |                    |          |
|-----------------------------------------------------------------------------|-----------------------------------|--------------------|----------|
| BPI Pain Severity                                                    | Relaxation
Acupressure
N=46 | Usual Care
N=43 | P-value* |
|                                                                             | Mean $\pm$ STD                    | Mean $\pm$ STD     |          |
| Baseline Pain Severity                                                      | 4.8 $\pm$ 1.6                     | 4.6 $\pm$ 1.8      | 0.51     |
| Week 6 Pain Severity                                                        | 3.5 $\pm$ 2.2                     | 4.6 $\pm$ 2.1      | 0.02     |
| Week 10 Pain Severity                                                       | 3.8 $\pm$ 2.2                     | 4.6 $\pm$ 2.2      | 0.10     |
| Point Change at 6 Weeks                                                     | -1.3 $\pm$ 2.0                    | 0.1 $\pm$ 2.0      | 0.003    |
| Point Change at 10 Weeks                                                    | -1.0 $\pm$ 1.8                    | 0.02 $\pm$ 1.6     | 0.006    |
| Percentage Change at 6 Weeks                                                | -27.2 $\pm$ 48.8                  | 20.2 $\pm$ 122.3   | 0.002    |

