## **6 TREATMENT PLAN**

### **6.1 Study Overview**

Participants with AIMSS will be randomized 1:1 to either true or sham self-acupressure interventions. Participants will use the provided modified MeTime Acupressure mobile app and AcuWand to self-administer acupressure daily for 12 weeks. All participants will complete weekly pain questionnaires, every 6-week symptom assessment batteries, and will be asked to provide optional stool samples for microbiome assessment prior to study entry and at 12 weeks. Participants randomized to the sham treatment will have the option of receiving the app with the true acupressure points after completion of the 12 week study intervention.

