### **6.2 Acupressure intervention**

Self-acupressure interventions (true and sham) will be delivered using our modified MeTime Acupressure mobile app. The MeTime Acupressure app has been renamed “Study App” and the icon changed so participants will not be able to locate it in the Apple or Google Play Stores and unblind

themselves. The sham and true acupressure apps are identical in all aspects except for the acupoint locations. The acupressure app will be loaded onto computer tablets by our computer information technology (IT) support person and provided to participants. Participants will also receive an AcuWand to be used in association with the acupressure app to help apply pressure to acupoints. The participants will receive directions within the acupressure app on how to use the AcuWand. Of note: our IT support person will be available to help participants who are unfamiliar with or have any issues with their tablet or the app.

**True Acupressure.** The true acupoints in this trial are identical to the relaxing acupressure acupoints that have been studied in prior trials, as described in the background section. There are 5 acupoints with 4 of the acupoints performed on both the left and right sides of the body (total of 9 points to stimulate). Each of the 9 acupoints will be stimulated for 3 minutes per point with the AcuWand giving a total treatment time of 27 minutes daily. The relaxation acupoints are:

- *Yin tang* (Unilaterally): forehead, between eyebrows
- *Anmian* (EX17) (Bilaterally): posterior aspect of the neck
- Heart 7 (HT7) (Bilaterally): palmer surface of the hands on the wrist crease
- Spleen 6 (SP6) (Right and Left/bilaterally): inside of the lower leg
- Liver 3 (LV3) (Bilaterally): foot

The true points were selected based on existing data showing their effectiveness for treating pain and fatigue.

**Sham Acupressure.** Sham acupoints were selected in locations where no known acupoints exist. There are 5 acupoints with 4 of the acupoints performed on both the left and right sides of the body (total of 9 points to stimulate). None of these points are on meridians nor are they near actual points (at least one inch away from meridians and points). They were chosen to be in the same general body quadrant as the relaxation points. Each of the 9 acupoints will be stimulated for 3 minutes per point giving a total treatment time of 27 minutes daily. The sham acupoints are:

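### The adherence endpoint is number of days, but the only between-arm adherence test is on a yes/no split; testing days directly would be a cheap improvement (optional)

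*Protocol*

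**What the plan says.** The Study Summary words the third secondary objective as a comparison of arms: "To examine the adherence with 12 weeks of true acupressure versus sham acupressure in patients with breast cancer taking aromatase inhibitor therapy". Section 1.2 gives its endpoint as "Number of days acupuncture is performed during the 12 weeks of the intervention". That section writes acupuncture throughout; I read it as acupressure, the intervention described everywhere else.

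The analysis is item 4 of the secondary endpoints (headed 12.3.2, inside section 11.3). It says "Adherence to the intervention will be assessed through the trial and reported using descriptive statistics", then "Adherence will be calculated based on number of days acupressure is performed and number of minutes of acupressure performed each day", and then names one test: "The proportion of participants who are fully adherent will be compared between groups using a chi-square test".

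No other part of the protocol compares days between arms. Item 3 of the same section applies t tests and GEE models to the remaining patient-reported outcomes and lists the domains; adherence is not among them. Section 11.3.1 does promise a description of all outcome variables by treatment group, so days will be summarised in each arm.

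The regimen is to "self-administer acupressure daily for 12 weeks" (section 6.1), with nine points "giving a total treatment time of 27 minutes daily" (section 6.2). Adherence comes from an electronic diary, and section 6.5 says that failing to complete it is not a deviation.

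**The concern.** The objective asks whether adherence differs between arms and measures it as a count from 0 to 84. The one test named answers a related but different question: whether the arms differ in the share of participants above some line. Two participants on the same side of that line count alike, however far apart their days are. If the line is every day, someone who stops in week 2 and someone who completes 83 of 84 days are both simply not fully adherent.

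What is at stake is modest. A reader of a self-administered, sham-controlled trial will want to know whether the two arms did the same amount of acupressure. A direct estimate of the difference in days, with its uncertainty, answers that better than a test on a split.

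**Working it through.** **Plan's own figure.** The protocol gives no power figure for adherence. Its only one is for worst pain (section 11.2): 80% power for 2 points, SD 2.3, 22 evaluable per arm, 5% level. A two-sided two-sample t-test with d = 2/2.3 = 0.87 and 22 per arm gives 80.4%, so that figure reproduces. I take 22 per arm from there.

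**Inputs for the illustration**
- Days possible: 12 × 7 = 84 (section 6.1).
- Reference adherence: 79.8 ± 22.9%, from the prior study in section 2.2 (42 sessions). On 84 days that is 0.798 × 84 = 67.0 days, SD 0.229 × 84 = 19.2 days.
- Other arm's mean: an assumption, set at 70%, 65% or 60% with the same SD. The gaps are (0.798 − 0.70) × 84 = 8.2 days, then 12.4 and 16.6 days. No document figure supports any particular gap.

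**Model.** Each participant's daily probability p is beta-distributed and days ~ Binomial(84, p). The beta parameters come from k = m(1 − m)/s² − 1, a = mk, b = (1 − m)k.
- m = 0.798, s = 0.229: k = 0.1612/0.0524 − 1 = 2.07, a = 1.66, b = 0.42.
- m = 0.65: k = 0.2275/0.0524 − 1 = 3.34, a = 2.17, b = 1.17.

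**Check on the model.** In the prior study "53 out of 74 women (72%) completed at least 70% of their acupressure treatments". Seventy percent of 84 is 58.8, so the matching cut is 59 days; the model puts 73.7% of the reference arm there. The agreement is good enough for an illustration.

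**Results.** Power from 4,000 simulated trials per row, two-sided 5%, uncorrected chi-square:

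| Assumed means | Rank-sum on days | Welch t on days | χ², all 84 | χ², ≥80 | χ², ≥76 | χ², ≥68 | χ², ≥59 |
|---|---|---|---|---|---|---|---|
| 79.8% v 70% | 42% | 30% | 33% | 42% | 38% | 29% | 20% |
| 79.8% v 65% | 67% | 53% | 47% | 68% | 65% | 55% | 41% |
| 79.8% v 60% | 87% | 78% | 52% | 85% | 85% | 79% | 66% |

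The Monte Carlo standard error is about √(0.67 × 0.33/4000) = 0.7 percentage points. Repeat runs differed by about 1 to 2 points; the middle row, for example, also came out as 68% for the rank-sum and 46% for the chi-square at all 84 days.

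**Reading the table**
- Literal reading (all 84 days): the loss against the rank-sum is 42 − 33 = 9, 67 − 47 = 20 and 87 − 52 = 35 points.
- Loose cut (≥59 days): the loss is 22, 26 and 21 points.
- Cut near 80 days: the loss is nil to 2 points, and the chi-square beats the Welch t-test.
- At a smaller gap (79.8% v 75%), all powers are low and close: rank-sum 15%, chi-square at all 84 days 16%.

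Under the literal reading about 17.8% of the reference arm qualifies, so the expected count is 0.178 × 22 = 3.9. That is small, but with equal arms the simulated rejection rate was 5.4%, so the test's size is not the problem.

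**The case against.** The best defence is that the endpoint is not neglected. Days are described by arm under section 11.3.1 and item 4, and the objective only says it will examine adherence, whereas the pain and symptom objectives say they will determine an effect. On that view a description plus one supplementary test is enough. It stands in part: the endpoint is reported. It does not explain why, once a between-arm test was chosen, it was put on a different variable.

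Three stronger readings are tempting, and the documents do not support them.
- *The cut-off is undefined, so it could be picked after seeing the data.* The protocol gives no cut-off, but such a threshold is commonly set in the statistical analysis plan, which is not shown here. Its absence is not a finding.
- *The split always wastes information.* It does not: at cuts near 80 of 84 days, a plausible meaning of full adherence, the chi-square matches the rank-sum.
- *Differential adherence is a main rival explanation of the primary result.* The two apps differ only in acupoint location and ask for the same daily time (section 6.2). Section 6.5 calls the analysis intent to treat, and nothing suggests that adherence will differ by arm.

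It is also fair that a test on days has limits of its own: it needs a rule for unrecorded diary days, and its power is about 42% for an 8-day gap.

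**Conclusion.** The mismatch is real and minor. The protocol sets number of days as the endpoint for a between-arm objective, and its only between-arm test is on a dichotomised quantity. In the illustration, for 80% versus 65%, the power cost runs from none (cut near 80 days) to about 20 points (all 84 days) or 26 points (59 days or more). Those sizes rest on prior adherence over 42 sessions carried over to 84 days, a beta-binomial model, equal SDs and assumed gaps, so they show direction and dependence on the cut-off rather than a forecast. This is a secondary endpoint and the primary analysis is untouched. I would rate the change as optional.

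**What to change.** In item 4, make the comparison of number of days performed (0 to 84) the between-arm analysis: a Wilcoxon rank-sum test, which the protocol already uses for the microbiome endpoints, with the difference in days and its 95% confidence interval (for example the Hodges-Lehmann estimate). State how unrecorded diary days count. Keep the proportion *fully adherent* as supportive description.

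The cost is a sentence or two; the diary data are already being collected. The small downside is that a missing-diary rule must be settled before analysis. The result also needs careful wording: by a t-test on days, 22 per arm has 80% power only for a gap of about 0.865 × 19.2 = 16.6 days. The interval should therefore carry the interpretation, and a non-significant test should not be read as balanced adherence.
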